#### Recruitment {15}

Our patients will be selected from the cases referring to a specialized CF clinic, which covers all the CF patients in our regional state. These patients are also supported by the Local CF Association. The initial data are available on the CF registry. As a result, access to the patients and their follow-up will be easier.

### Assignment of interventions: allocation

#### Sequence generation {16a}

The patients meeting the inclusion criteria will be enrolled in the study. Initially, stratified randomization will be used to divide the participants into two groups based on disease severity (severe/mild-to-moderate) using spirometry with 40% FEV1 cutoff range. Following that, random sampling will be applied to select the patients from each group to be administered with the nano-curcumin drop or nano-curcumin placebo drop using a random number table (Fig. 1).

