### Eligibility criteria {10}

#### Inclusion criteria

The inclusion criteria of the study are as follows: (1) one or more typical phenotypic features of CF and a minimum of an elevated sweat chloride concentration on two/more occasions or two mutations known to cause CF on separate alleles; (2) age of 5–18 years; (3) pulmonary and gastrointestinal involvement; (4) ability to perform spirometry maneuvers and the minimum FEV1 of ≥ 30% compared to the same age, gender, and height in the normal population; (5) the percentage of oxygen saturation based on pulse the oximetry of ≥ 90% at room temperature; and (6) informed consent for participation.

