#### Exclusion criteria

The exclusion criteria of the study are (1) cardiovascular, hepatic, and renal failure; (2) celiac disease and rheumatoid arthritis; (3) acute pulmonary exacerbation requiring hospitalization within the past 4 weeks; and (4) acute respiratory tract infection.

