#### Statistical methods for primary and secondary outcomes {20a}

Data analysis will be performed in SPSS version 16, and data distribution will be evaluated using the Kolmogorov-Smirnov test. Data are expressed as frequencies for the qualitative variables, mean and standard deviation for the normally distributed continuous variables, and median and interquartile range for the other variables. In addition, intergroup differences will be evaluated using paired t-test for the normally distributed continuous variables and Wilcoxon rank-sum test for the other variables. Intragroup differences will be assessed using independent *t* test for the normally distributed continuous variables and Mann-Whitney *U* test for the other variables. The mean changes in the secondary outcomes will also be adjusted for the baseline data and disease severity using the analysis of covariance (ANCOVA). In all the statistical analyses, the *P* value of ≤ 0.05 will be considered significant.

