#### Methods for additional analyses (e.g., subgroup analyses) {20b}

The baseline data and disease severity will be controlled using ANCOVA or binary logistic regression.

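### The 40% FEV1 split leaves a severe stratum only 10 points wide; if that two-level factor is the severity covariate, most lung-function information goes unused, and continuous baseline FEV1 would recover it at no cost

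*Protocol article*

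**What the plan says.** Three parts of the protocol article bear on this.

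- **Entry.** The inclusion criteria require "ability to perform spirometry maneuvers and the minimum FEV1 of ≥ 30% compared to the same age, gender, and height in the normal population". No upper limit on FEV1 is set. They also set a saturation floor ("the percentage of oxygen saturation based on pulse the oximetry of ≥ 90% at room temperature") and an age range ("age of 5–18 years"). The exclusion criteria remove children with "acute pulmonary exacerbation requiring hospitalization within the past 4 weeks".
- **Randomisation.** Sequence generation {16a} uses stratified randomisation to "divide the participants into two groups based on disease severity (severe/mild-to-moderate) using spirometry with 40% FEV1 cutoff range". Severity is the only stratification factor. No reason for 40% and no expected stratum sizes are given.
- **Analysis.** Section {20a} says that mean changes in the secondary outcomes will be "adjusted for the baseline data and disease severity using the analysis of covariance (ANCOVA". Section {20b} adds: "The baseline data and disease severity will be controlled using ANCOVA or binary logistic regression". Neither section says how severity is coded. Section {16a} is the only place that defines it.

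**The concern.** Severity of lung disease is the one factor on which the trial balances its arms, and it is named again as an adjustment variable. A two-level factor does that job well only if it divides the children into groups that differ substantially and are both reasonably filled. Here the lower group is a 10-point band just above the entry floor. A child at 42% and a child at 105% count as equally severe, while children at 38% and 42% do not.

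If the same factor is carried into the analysis, the arms could be perfectly balanced on it and still differ noticeably in mean FEV1, and adjusting for it would remove little of that difference. What is at stake is precision, and freedom from chance imbalance, in adjusted comparisons of quality of life, BMI z-score and any inflammatory marker analysed under {20b}.

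**Working it through.** **Inputs from the protocol.** FEV1 floor 30% (inclusion criteria); stratum cut 40% ({16a}); 60 children, 30 per arm ({14}). The cut is read as percent predicted, like the floor. The protocol states no stratum size and no FEV1 distribution, so it has no figure of its own to reproduce.

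**Assumption.** FEV1 is normal with mean m and SD s, truncated at 30%. Four (m, s) pairs span a mildly to a heavily affected clinic.

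**Step 1, width of the band.** 40 − 30 = 10 points. The other stratum is everything from 40% upward.

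**Step 2, share in the severe stratum.** p = [Φ((40 − m)/s) − Φ((30 − m)/s)] / [1 − Φ((30 − m)/s)]

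- m = 85, s = 20: (0.0122 − 0.0030)/0.9970 = 0.9%; × 60 = 0.6 children
- m = 75, s = 22: (0.0558 − 0.0204)/0.9796 = 3.6%; × 60 = 2.2
- m = 65, s = 22: (0.1279 − 0.0558)/0.9442 = 7.6%; × 60 = 4.6
- m = 55, s = 20: (0.2266 − 0.1056)/0.8944 = 13.5%; × 60 = 8.1

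As a check on the normal shape, a uniform spread over 30-100% gives 10/70 × 60 = 8.6. At the other extreme, mean 90 with SD 15 gives practically none.

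**Step 3, FEV1 variance captured by the split.** R² = p(1 − p)(μ_upper − μ_lower)²/σ², where the means and σ are those of the truncated distribution. For m = 75: 0.0361 × 0.9639 × (77.6 − 35.7)²/20.8² ≈ 0.14.

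**Step 4, room left for chance imbalance.** With 30 per arm, the 95% limit for the between-arm difference in mean FEV1 is 1.96 × σ × √(2/30) without stratification. It is that figure times √(1 − R²) if the strata are perfectly balanced. For m = 75: 1.96 × 20.8 × 0.258 = 10.5 points, and 10.5 × √(1 − 0.14) = 9.8 points.

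| Assumed mean, SD | Severe, of 60 | σ after truncation | R², 40% cut | R², median cut | 95% limit: no strata | 40% cut | median cut |
|---|---|---|---|---|---|---|---|
| 85, 20 | 0.6 | 19.7 | 6% | 64% | 10.0 | 9.7 | 6.0 |
| 75, 22 | 2.2 | 20.8 | 14% | 65% | 10.5 | 9.8 | 6.2 |
| 65, 22 | 4.6 | 19.6 | 22% | 66% | 9.9 | 8.8 | 5.8 |
| 55, 20 | 8.1 | 16.8 | 31% | 66% | 8.5 | 7.0 | 5.0 |

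The 40% split narrows the limit by about 3-17%. A continuous FEV1 covariate retains all the FEV1 information in the analysis. The median cut is shown only as a yardstick for a two-level factor.

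**Step 5, what the planned models already cover.** {20a} and {20b} name baseline data as well as severity. Read as each outcome's own baseline, this includes baseline FEV1 when the outcome is spirometry. It does not bring FEV1 into a model for quality of life, BMI z-score or an inflammatory marker. There the severity term is the only carrier of lung function.

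**The case against.** Several points on the other side stand.

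- **The stratum size is not known.** Every count above rests on an assumed distribution. Inclusion also requires pulmonary involvement, which makes the high-mean scenarios less likely, and the exacerbation exclusion is time-limited, so it need not thin the severe group for good. The investigators have registry data ({15}) and may know the split. A reader might infer that the stratum is bound to be almost empty; the protocol does not establish that.
- **The covariate may not be two-level.** {20a} and {20b} do not say so. The point is therefore conditional, although the only definition on offer is the 40% split.
- **Own-baseline adjustment does much of the work.** It deals with spirometry directly and with part of the variation in the other outcomes. A reader might infer that the planned adjustment controls almost nothing. Even the split alone captures 6-31% of FEV1 variance in the four scenarios, so that goes too far.
- **FEV1 variance is not outcome variance.** The protocol does not say how strongly FEV1 predicts changes in IL-6, IL-10, hs-CRP, calprotectin or quality of life. Chance imbalance is not bias and is reflected in the standard error. The loss in precision for any endpoint cannot be calculated from the document.
- **A severity-based cut has a legitimate purpose.** It keeps a few severe children from all landing in one arm. A median cut would be another dichotomy with its own adjacent-value problem.

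None of this argues against using the continuous measurement in the analysis.

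**Conclusion.** The point holds as a conditional weakness with a free remedy. What the text fixes is certain: severe means 30-40% predicted, and all other children form one stratum. The size is an estimate. Under truncated-normal FEV1 with mean 55 to 85 and SD 20 to 22, about 1 to 8 of 60 children are severe and the split captures about 6-31% of FEV1 variance; distributions further out would widen this in both directions. If the two-level factor is the severity covariate, most lung-function differences between arms stay unadjusted for outcomes other than spirometry. How much that matters for each endpoint is unknown.

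Two stronger readings are not supported. The 30% floor and the 40% cut do not contradict each other, since any stratification cut has to lie inside the eligible range. Nor does the protocol show that 40% is the wrong cut: keeping or moving it is a design trade-off.

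**What to change.** In {20a} and {20b}, state that the ANCOVA and logistic models adjust for baseline FEV1 % predicted as a continuous covariate together with the outcome's own baseline value, instead of relying on the severe/mild-to-moderate factor. Where the outcome is FEV1 itself, the two terms coincide and enter once. The stratum indicator may stay in the model as the randomisation factor, provided it is not the only lung-function term.

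The cost is analysis wording only. FEV1 is measured on every child at entry, so no patients, visits or procedures are added, and the change can be made after randomisation has started as long as it precedes any look at unblinded data. A linear FEV1 term is a modelling assumption, but a milder one than treating everyone from 40% upward as alike.

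Optionally, before randomisation, read the expected stratum sizes from the registry mentioned in {15} and report them with the reason for the 40% cut. Changing the cut in light of them is for the authors to decide.

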**Fig. 1 Fig1:**
[figure not shown]
Schematic of study design. First and second evaluations consist of the following: serum interleukin-6 (IL-6), IL-10, and high sensitivity. C-reactive protein (hs-CRP), fecal calprotectin, weight and body mass index (BMI), and score of quality of life of the cystic fibrosis questionnaire (CFQ)

#### Concealment mechanism {16b}

The random number table is used to select the patients from each group following stratified randomization based on disease severity. In addition, a random sequence is printed and placed inside envelopes by an individual other than the trial researchers. The envelopes will be randomly selected by the patients, so that they would be assigned to the intervention or control groups based on the contents of the selected envelope. Curcumin and placebo labeling has also been provided by Exir Nano Sina Company.

#### Implementation {16c}

Generation of the allocation sequence, enrollment of participants, and assignment of participants to interventions will be done by the main researcher of the trial.

### Assignment of interventions: blinding

#### Who will be blinded {17a}

Curcumin and placebo glasses have been labeled A and B by Exir Nano Sina Company, respectively, and are made available to the patients through the double-blind design of the trial. Notably, the participants and researchers are unaware of the groups assigned to the patients, while the data analysts are not blinded to the trial.

#### Procedure for unblinding if needed {17b}

Although we do not anticipate any requirement for non-blinding, the trial manager, data coordinator, implementation support facilitators, participants, and researchers will have access to group allocations, and possible non-blinding will be reported.

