### Trial design {8}

This is a prospective, single center, double-blind, parallel, randomized placebo-controlled clinical trial. The study protocol was written following the standard Protocol Items Recommendation for Interventional Trials (SPIRIT) Checklist (Table 1).

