#### Intervention description {11a}

Nano-curcumin (Exir Nano Sina Drug Company, Iran) is prepared as nano micelle in the form of 70 mg of drops in 1 cc, and the placebo with the same color, taste, and odor.

To adjust the drug dose for different ages and considering that the maximum acceptable dose based with the most significant impact and minimum side effects was 80 mg, the required amount will be obtained for each subject based on the ratio of the body surface area of the patients. The curcumin and placebo glasses have been labeled A and B by Exir Nano Sina company, respectively, and made available to the patients through a double-blind design. Curcumin or placebo will be administered orally alone or with sweetened water once daily at bedtime and at a fixed dose for 3 months.

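### The double-blind claim is contradicted by the protocol's own text: {17a} and {17b} disagree on who knows the allocation, and the A/B bottle code is printed with its key

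*Protocol article*

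**What the plan says.** All references are to the protocol article.

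- **Trial design {8}** describes a "single center, double-blind, parallel, randomized placebo-controlled clinical trial".
- **Intervention description {11a}** says: "The curcumin and placebo glasses have been labeled A and B by Exir Nano Sina company, respectively". It also says that the placebo is matched in appearance, flavour and smell.
- **Who will be blinded {17a}** repeats the labelling ("Curcumin and placebo glasses have been labeled A and B by Exir Nano Sina Company, respectively"). On who knows the arms, it says that "the participants and researchers are unaware of the groups assigned to the patients, while the data analysts are not blinded to the trial".
- **The section on unblinding {17b}** opens with "Although we do not anticipate any requirement for non-blinding". It then lists the trial manager and data coordinator, and says that "implementation support facilitators, participants, and researchers will have access to group allocations". It closes by saying that any unblinding will be reported.

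**The concern.** Two adjacent sections give opposite answers about the same two groups of people. The double-blind label depends on the first answer, and staff who followed the second would break the blind. Separately, the labelling uses one letter per treatment arm and the article prints what each letter means. A matched placebo cannot protect the blind of someone who can read the letter and has read the protocol.

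At stake are the outcomes and decisions that respond to expectation or effort. These are the CFQ completed by child and parent, spirometry, and the judgement under {11b} that a side effect is intervention-related or that a reported deterioration should end treatment. Nurses and assistants acting as trial researchers collect the data (Data management {19}), and {17b} gives researchers access to the allocations. A blind lost during follow-up cannot be restored at the analysis.

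**Working it through.** No formula applies and the plan gives no figure to reproduce. The check compares the sections.

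**1. Who knows the allocation?**

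| Group | {17a} | {17b} |
|---|---|---|
| Participants | unaware | have access |
| Researchers | unaware | have access |
| Trial manager, data coordinator, facilitators | not mentioned | have access |
| Data analysts | not blinded | not mentioned |

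The first two rows conflict. A code-break procedure would reconcile them if {17b} said what event opens the code, who holds it, and that it is opened for one participant at a time. The sentence says none of these. Its opening clause says only that unblinding is not expected, and the grant of access that follows carries no condition.

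**2. What does the bottle reveal?** {11a} and {17a} both name curcumin and placebo in that order, then A and B in that order, and add *respectively*. The mapping is therefore A = curcumin and B = placebo. It appears in a published article that families and staff can read.

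**3. How far does one disclosure spread?** The code has two values for 60 children (30 per group, Sample size {14}).

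- With one letter per arm, a person who learns what one letter means can classify every child whose letter that person knows. For someone who has seen all the bottles, this reaches 60 of 60.
- With participant-unique kit numbers, opening one code reveals 1 of 60.
- A family that learns the meaning of A learns its own child's arm, and others only if letters are compared. All patients attend one clinic and are supported by one local CF association (Recruitment {15}), so comparison is possible, but the document gives no basis for estimating how often it would happen.

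**4. Which outcomes are exposed?**

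- *More exposed:* the CFQ is self- or parent-reported, and spirometry depends on effort and coaching. Both are secondary outcomes (Outcomes {12}).
- *Less exposed:* serum IL-6, IL-10 and hs-CRP, and fecal calprotectin, are primary outcomes. They are run in duplicate by laboratory staff ({18a}) on specimens carrying a coded ID ({27}).
- *Indirect route:* outcomes are measured only at baseline and at 3 months, and {20c} carries the last observation forward. A child who stops and has no 3-month measurement would thus be assigned a change of zero on every outcome. If knowledge of the arm influenced who stops, this could reach the laboratory outcomes too. It arises only where stopping leads to a missing measurement, since {20c} keeps non-adherent participants in the analysis.

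**5. What can unblinded analysts influence?** Statistical methods {20a} names a normality test and assigns t-tests or rank tests according to the result. The selection rule is stated, and a normality check does not look at the treatment effect. Knowing the arms gives some room for discretion, but less than an open choice of test would.

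**The case against.** The strongest defence is that {17b} should be read under its heading. The section concerns unblinding if it is needed, opens by saying none is expected, and ends by promising to report any that occurs. Standing access for participants would make that promise pointless and would contradict {8}, {11a} and {17a}. On this reading the sentence lists who may be told the allocation if unblinding is required, or is simply badly worded. This stands as a plausible account of what was intended, so the text shows a contradiction and not a plan to reveal allocations. It does not remove the problem. The written sentence is unconditional, a list that includes all participants and researchers is not a code-break procedure, and the printed A/B key is untouched by it.

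Four stronger inferences are tempting, and the document does not support them:

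- *That the blind cannot hold.* The text does not support the double-blind claim as written, but it does not show that the blind was or must be lost.
- *That the bottles carry nothing but the letter.* The letter is the only label described; the article does not exclude others. An added number would not help, however, while the letter stays visible.
- *That one disclosure unblinds all 60 children.* This is the worst case and requires knowing every child's letter.
- *That unblinded analysts are an error.* The article states openly that "the data analysts are not blinded to the trial". Blinding of participants and researchers does not depend on the analysts. Blinding them too would be good practice, not the correction of a mistake.

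**Conclusion.** The concern holds in this form: the protocol's double-blind claim is contradicted by its own wording on access to allocations, and is weakened by a one-letter-per-arm code whose key is printed twice. Both points rest on the text alone and need no assumption about conduct.

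The size of any bias cannot be derived from the document. The structural contrast is up to 60 of 60 participants exposed by one disclosure, for a person who knows all the letters, against 1 of 60 with unique kit numbers. The risk lies mainly with the CFQ, spirometry and stopping judgements. The laboratory primary outcomes are less exposed, apart from the indirect route through stopping and missing 3-month data. The correction should be made before participants are treated, because it cannot be made afterwards.

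**What to change.** 1. **Reconcile {17a} and {17b}.** Delete the statement that participants and researchers have access to allocations. Replace it with a code-break for a single participant, held outside the research team, and state who holds it, what opens it and how each use is recorded.
2. **Replace the visible code.** Over-label the bottles with participant-unique kit numbers that hide the A/B letter. Have the manufacturer, or a pharmacist outside the team, hold the kit-to-treatment list. Remove the A/B mapping from working documents.
3. **As an improvement, blind the analysts.** Supply dummy group codes that differ from the bottle letters until the database is locked and the primary analysis has been run.

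The cost is relabelling the bottles of about 60 participants, a person to hold the list, and changes to the protocol wording. Analyst blinding needs only a recoded group variable. If the bottles have already been supplied with letters, over-labelling is still possible.

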### Data collection and management

#### Plans for assessment and collection of outcomes {18a}

As the primary outcome of the present study, blood vessel inflammation will be assessed in the sample using the ELISA assay (IL-6, IL-10, and hs-CRP), stool inflammation will be determined by measuring the calprotectin level using the ELISA assay, and pulmonary inflammation will be evaluated using the smear and culture (gram-positive, gram-negative, pseudomonas) of the nasopharyngeal soap. All the tests will be performed at the Buali Research Institute by expert personnel. Table 2 shows the performance specifications of the applied methods.

For the quality assurance of the employed laboratory methods, the performance specifications will be verified before using the kits for the analysis of the patient samples. All the tests will be performed in duplicate, and the standard curve will be prepared using the serial dilutions of the standard samples. The obtained results will be calculated from the standard curve after adjustment for the blank.

The secondary outcome of the present study was anthropometric assessment, which will be performed in a standard position using SECA instruments for height and weight. In addition, the WHO growth standard charts will be used for the evaluation of the BMI *z*-score.

In the current trial, we will apply the CFQ-R to assess the effects of nano-curcumin on the quality of life of the children with CF. The CFQ was first developed in France and consists of three appropriate versions for children aged 6–13 years (CFQ-child), as well as the parents of children with CF aged 6–13 years (CFQ-parent) and adolescents and adults with CF aged 14 years (CFQ-teen/adult) [28]. After the psychometric assessment of the original version and slight modifications, the final version of the CFQ-R was developed.

Spirometry will be performed using a spirometer (CHESTGRAPH HI-105), with the patients in a stable, standing position and their neck completely straight. To increase accuracy and reliability, the test will be repeated at least twice. If FVC and FEV1 are more than 150 ml different from the first time, the test will be repeated; the maximum repetition will be eight times.

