#### Outcomes {12}

The primary outcomes of the current trial are the compared changes in the blood vessel inflammation, nasopharyngeal swab, and fecal samples at baseline with 3 months after the intervention: systemic inflammation by assessing IL-6 as an inflammatory agent, IL-10 as an anti-inflammatory agent, and hs-CRP level in the blood samples, pulmonary inflammation with the neutrophil count, bacterial/viral culture on the nasopharyngeal swab, and gastrointestinal inflammation with the calprotectin level in the fecal samples.

The secondary outcomes are changes in clinical assessment of the pulmonary symptoms via spirometry, anthropometric assessment stand on the BMI Z score, and evaluation of the quality of life using the CFQ from the baseline to 3 months of the intervention.

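### The spirometry repeat rule compares with the first blow, links FVC and FEV1 by 'and', and uses one 150 ml limit for all children: a minor defect, cheap to correct

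*Protocol article*

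**What the plan says.** The rule is in the protocol article, Plans for assessment and collection of outcomes {18a}. It sets a minimum number of efforts, "To increase accuracy and reliability, the test will be repeated at least twice", and then gives a trigger for further blows together with a cap: "If FVC and FEV1 are more than 150 ml different from the first time, the test will be repeated; the maximum repetition will be eight". The only stated consequence of exceeding 150 ml is another blow. The section does not say that a session is rejected, or which blow is recorded.

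Spirometry has three uses in this trial:

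- **Eligibility.** The Inclusion criteria admit "age of 5–18 years", the ability to perform spirometry, and "the minimum FEV1 of ≥ 30% compared to the same age, gender, and height in the normal population".
- **Stratification.** Sequence generation {16a} splits children by severity at 40% FEV1.
- **Outcome.** Outcomes {12} lists as secondary the "changes in clinical assessment of the pulmonary symptoms via spirometry" over 3 months.

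Statistical methods {20a} also names disease severity as an ANCOVA covariate for the secondary outcomes.

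**The concern.** Three features of the sentence work badly if staff apply it as written.

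1. **Reference blow.** Repeatability is judged against the first effort, not among the best efforts. If the first is poor and the later ones are better and agree with each other, the condition still fails. A child who reproduces a poor first effort passes.
2. **Conjunction.** Taken literally, a repeat is due only when FVC and FEV1 both differ. A large discrepancy in one index is accepted if the other agrees.
3. **Flat limit.** One absolute tolerance covers young children and adolescents, with FEV1 down to 30% of normal. In a small or severely affected child, 150 ml can be a large part of the measured value.

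At stake are the precision of the lung-function outcome and, for children near 30% or 40% FEV1, correct entry and stratum. The last point assumes that the same procedure is used at screening; the article describes no other.

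**Working it through.** The plan derives no figure from this rule, so there is none to reproduce. Four checks follow.

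**1. Poor first blow, worked example (made-up values).** FEV1 is 1.20 L, then 1.50 to 1.54 L. FVC is 1.50 L, then 1.85 to 1.89 L. The smallest differences from the first blow are 1.50 − 1.20 = 0.30 L and 1.85 − 1.50 = 0.35 L, both above 0.150 L. The rule is never met within eight blows, whether 'and' is read literally or as 'either'. The two largest blows agree by the third.

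**2. Poor first blow, simulation.** Assumption: each blow falls below the child's maximum by a half-normal amount with scale 60 ml, and the first falls a further fixed deficit below. Checked: whether any of blows 3 to 8 lies within 150 ml of blow 1, on FEV1 only.

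| Extra first-blow deficit | Rule unmet after eight blows |
|---|---|
| 0 ml | about 0% |
| 100 ml | about 3% |
| 200 ml | about 47% |
| 300 ml | about 98% |

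The two best of the first three blows agree within 150 ml in over 99% of these sessions. Sensitivity at the 200 ml deficit:

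- Scale 30 ml: unmet in 85%; scale 100 ml: 31%. The two-best comparison is met by blow 3 in 100% and 92%.
- Literal 'and' (same deficit in FVC, independent noise): 47% falls to about 22%.
- Counting blows 2 to 9, because eight repetitions can mean nine blows: about 40%, or about 16% with literal 'and'.

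**3. Literal 'and' (made-up values).** FVC is 2.00, 1.60, 1.60 L and FEV1 is 1.50, 1.48, 1.45 L. The FVC gap is 0.40 L and the largest FEV1 gap 0.05 L. Literally read, no repeat is due. If either index suffices, one is.

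**4. Flat limit.** The documents give no lung volumes, so predicted FEV1 is assumed to lie between 1.0 and 4.0 L. Tolerance in percent-predicted points = 100 × 0.150 / predicted FEV1. Share of measured FEV1 = 0.150 / (predicted FEV1 × fraction of predicted).

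| Assumed predicted FEV1 | Points | Share at 30% predicted | Share at 40% | Share at 100% |
|---|---|---|---|---|
| 1.0 L | 15 | 50% | 37.5% | 15% |
| 1.5 L | 10 | 33% | 25% | 10% |
| 2.0 L | 7.5 | 25% | 19% | 7.5% |
| 4.0 L | 3.8 | 12.5% | 9.4% | 3.8% |

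The entry limit and the stratum cut-off are 40 − 30 = 10 points apart. At 1.5 L predicted the tolerance equals that gap, and at 1.0 L it exceeds it.

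Comparing the two largest blows does not cure this by itself. With FEV1 0.36, 0.50, 0.40 L and FVC 0.60, 0.74, 0.62 L, both rules pass at blow 3, although the first two FEV1 values differ by 0.14 / 0.50 = 28% of the largest. A limit of, for illustration, 10% of the largest value would be 0.05 L. The two largest FEV1 values differ by 0.50 − 0.40 = 0.10 L, so a repeat would follow.

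**The case against.** The strongest reply is that the text attaches no harm to failing the rule except more blows. A reader might infer that a child who improves is penalised, or that poor baseline values are kept. The documents support neither: no session is rejected, and the recorded value is not stated. If the best value is kept, the extra attempts even help slightly. In the same simulation the best of eight blows averages about 10 ml below the child's maximum, against about 28 ml for the best of the first three. This stands: the cost of using the first blow as reference is mainly needless repeats.

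A reader might also infer that practice by month 3 creates a spurious treatment effect. The rule is the same in both randomised arms, so any practice gain is shared, and the ANCOVA adjusts secondary outcomes for baseline.

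The simulation figures are conditional. The 47% and 98% arise from assumed deficits above the 150 ml limit. How often such first blows occur is not given in the documents, and below the limit failure is rare. Nor do these figures show that the youngest or sickest children fare worst on this feature: deficits of 200 to 300 ml describe larger lungs.

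Finally, the wording may be loose English for agreement between blows, with 150 ml meant for each index. That is possible, but the sentence as printed fixes a reference blow, a conjunction and a limit, and staff would act on it. So this is a badly fixed rule, not an omitted detail.

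**Conclusion.** The point holds as a minor one. Using the first blow as reference can send a child with consistent later blows to the cap. The literal 'and' can accept a large gap in one index. The flat 150 ml is proportionally loose at low volumes. The first two follow from the sentence itself; their frequency depends on an unknown rate of poor first blows. The third is arithmetic over an assumed range of predicted FEV1.

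The expected consequences are needless repeats, extra noise in a secondary outcome and some misclassification near 30% and 40% FEV1. No bias between arms is to be expected, and neither the primary outcomes nor the sample size is affected.

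**What to change.** Replace the sentence in {18a} with a rule of this form. After at least three acceptable blows, repeat, up to the stated maximum, if the two largest FEV1 values **or** the two largest FVC values differ by more than 150 ml, or by more than a smaller, volume-scaled limit in children with low volumes. Apply the scaling to each index separately, so that a child with low FEV1 but FVC above 1 L is also covered. Use the largest FEV1 and the largest FVC at both visits. State whether the maximum of eight counts all blows or only the repeats.

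The scaled limit is for the investigators to set; the 10% above is only an illustration, since the documents give no basis for a figure. The change is one sentence, with the same device and staff. The downside is a few more blows in very small children, partly offset by fewer needless repeats after a poor first blow.
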